### 2.12 Statistical analysis plan

#### 2.12.1 Full analysis set

Statistical analysis will be conducted by a third-party statistical unit using SAS v9.4 software (SAS Institute, Inc.). The full analysis set (FAS) will be the data set as close as possible to the ideal set of subjects in compliance with the intention-to-treat principle, and all subjects who are randomized into the group and have more than one medication record and evaluation of its efficacy will be included in the FAS. Missing data will be imputed using the last observation carried forward (LOCF) method if there are efficacy values after randomization. The FAS will be used for primary efficacy analysis in this study, and all efficacy variables will be analyzed using the FAS.

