## 2 Methods and design

### 2.1 Study design and patient selection

The LONGAN trial is a prospective, multicenter, randomized, placebo-controlled, double-blind, parallel-group, superiority trial that enrolls patients from stroke and rehabilitation units in China. This study will be conducted at 15 sites across China. The primary objective of the trial is to test the hypothesis that LSZ capsule is superior to the placebo for increasing the proportion of favorable functional status, defined as a modified Rankin Scale (mRS) score ≤1 at 90 days. The secondary objective is the assessment of any other benefits or harms from the end of the treatment period up to 180 days after the stroke. Participants will be followed up at 30, 90 and 180 days after randomization (D30, D90 and D180, respectively) to collect efficacy and safety outcomes in person. Patient enrollment will begin in May 2022 and end in June 2023. Figure 1 presents a schematic diagram of the patient timeline. The trial was approved by the institutional review board of Dongzhimen Hospital, Beijing University of Chinese Medicine, Beijing, China and registered in public clinical trial database (No. 2021DZMEC-198-02; ClinicalTrials.gov Identifier NCT 05277311). We described this study protocol according to the SPIRIT 2013 Statement, and the complete checklist is available.

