### 2.2 Randomization, allocation, and blinding

Eligible patients who consent to participate will be assigned to the LSZ capsule experimental or control group at a 1:1 ratio using permuted block randomization stratified according to medical centers. The randomization program will be generated by an independent statistician using SAS software v9.4 (SAS Institute, Inc.; Cary, NC, United States) and stored in sealed, sequential, opaque envelopes. The site pharmacist will retain these envelopes, which will be assigned in the order specified by the statistician.

At randomization, study medications will be packaged into a large box containing LSZ capsules or LSZ placebo capsules. When the patient is discharged, the trial medication will be continued and documented on the discharge summary and on the patient’s list of ongoing medications. At 30 days after randomization, patients will be instructed to bring partial empty boxes to this follow-up. Patients who stop taking the allocated treatment early will be followed up, and their data will be included in the primary analyses. The reason for stopping the treatment prematurely, e.g., a SAE, will be recorded in the patient’s electronic case report form (CRF).

Active and placebo capsules with identical appearances, colors, and flavors will be prepared by Buchang Pharmaceutical Co, Ltd. The placebo capsules are visually identical to the LSZ capsules, even when broken open. In the study, each patient’s medications will be prepared as a unit-dose kit according to the predetermined randomization schedule. The site pharmacies will not disclose the randomization assignments unless information is required for patient treatment in exceptional circumstances. The clinical center pharmacist will be unblinded to the treatment, but all investigators, participants, caregivers, and data analysts will be blinded to treatment assignments throughout the trial until the blind codes are revealed. Investigators can request emergency unblinding in cases of serious adverse events (SAEs) suspected to be associated with the investigational medicine.

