### 2.3 Treatment

Eligible patients will be randomly assigned to the experimental and control groups. Participants in the experimental group will receive 5 LSZ capsule (0.4 g each), three times a day for 90 days. The control group will receive a LSZ placebo using the aforementioned protocol; the main ingredients of placebo including starch, dextrins, silicon dioxide, medical yellow iron oxide, caramel color liquid, and purified water will be identical to the LSZ capsule in appearance, weight, and taste. The treatment assignments are presented in Figure 2. All patients will receive a standard treatment, which is referred to in the current guidelines (Chinese Society of Neurology and Chinese Stroke Society, 2018; Powers et al., 2019), including antiplatelet therapy, control of vascular risk factors, and appropriate rehabilitation. During the trial, drugs with composition or efficacy similar to the study drug, such as CM decoctions (compound granules), CM injections, and Chinese patent medicine and health products, will not be permissible. Other concomitant medications will be allowed during the study, but these should be recorded in the subjects’ CRF during the trial. The study drug will be discontinued in cases of SAEs, request for study withdrawal by the patient or their legally authorized representative, or poor compliance or non-adherence to the prescribed interventions. We will truthfully record the reasons for stopping interventions.

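### The primary analysis set drops randomised patients with too few medication records or no efficacy evaluation, against the intention-to-treat principle it invokes and the promise to keep early stoppers

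*Protocol article*

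**What the plan says.** Section 2.12.1 (Full analysis set) describes the FAS as "as close as possible to the ideal set of subjects in compliance with the intention-to-treat principle" and gives its membership rule: randomised subjects who "have more than one medication record and evaluation of its efficacy will be included in the FAS". The same section fixes its role: "The FAS will be used for primary efficacy analysis in this study". On missing values it says: "Missing data will be imputed using the last observation carried forward (LOCF) method if there are efficacy values after randomization".

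Section 2.2 (Randomization, allocation, and blinding) says: "Patients who stop taking the allocated treatment early will be followed up, and their data will be included in the primary analyses". It sets no minimum exposure.

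Section 2.3 (Treatment) lists reasons for ending study drug, among them serious adverse events, withdrawal requests and poor compliance. Section 2.1 places the first visit after baseline at day 30: "Participants will be followed up at 30, 90 and 180 days after randomization". The only other efficacy set, the per-protocol set in Section 2.12.2, is narrower than the FAS. The article states no analysis of all randomised patients.

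**The concern.** The rule on who is in the FAS uses two facts that are known only after randomisation: how many medication records a patient accumulates, and whether efficacy was evaluated. Both can depend on the assigned treatment and on prognosis, for example through early intolerance, an early serious adverse event or early deterioration. Removing patients on such grounds gives up part of the protection that randomisation provides. It can also discard a patient whose D90 mRS, the primary outcome, is known.

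The article also gives two different answers on whether the earliest stoppers count in the primary analysis. If that is settled once allocation is known, it becomes a data-driven choice of the kind the Abstract and Discussion say this publication is meant to prevent.

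**Working it through.** **1. The passages side by side.** The FAS sentence lists who is in and offers no other way in.

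| Randomised patient | FAS rule, Section 2.12.1 | Section 2.2 | Result |
|---|---|---|---|
| Never started study drug | Out, even with a D90 mRS | Silent: it concerns patients who stop | Departs from intention to treat |
| Stopped after one medication record, D90 mRS known | Out | In | Direct contradiction |
| Stopped early, no efficacy evaluation | Out; nothing to carry forward | To be followed and included | Departs from intention to treat; conflicts with the promise of inclusion |
| Stopped early, two or more records and an evaluation | In | In | No conflict |

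Section 2.12.1 does not say when the efficacy evaluation must take place. After randomisation is the natural reading, since every patient is assessed at baseline (Section 2.7).

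**2. The looser reading.** Suppose *more than one* is meant as *at least one*. The second row then moves into the FAS. The first and third rows stay out.

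**3. The plan's own figures (Section 2.11).** Inputs: 60% versus 69% favourable, two-sided 5%, 90% power, 10% loss to follow-up.
- The usual two-proportion formula with continuity correction gives 1,228 in total, against 1,238 stated. Without the correction it gives 1,184.
- 1,238 / 0.90 = 1,375.6, rounded up to 1,376, as stated.
- Power = Φ[(0.09·√n − 1.96·√(2·0.645·0.355)) / √(0.60·0.40 + 0.69·0.31)]. At n = 619 per arm this is 91.2%. At n = 688 per arm (all 1,376) it is 93.8%.

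If 60% versus 69% holds, analysing everyone costs no power. The issue is bias and which patients the result describes.

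**4. Size of a possible bias (illustration only).** The article gives no exclusion rate, so the exclusion shares and the outcome among the excluded are assumptions. Let p be the true favourable rate in an arm, f the share excluded and r the favourable rate among the excluded. The rate seen in the FAS is (p − f·r) / (1 − f).

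Take no true effect (p = 0.60 in both arms) and r = 0.30.
- 6% of LSZ and 3% of placebo excluded: LSZ (0.60 − 0.018) / 0.94 = 0.6191; placebo (0.60 − 0.009) / 0.97 = 0.6093. Spurious difference 0.99 points.
- 8% and 4%: LSZ (0.60 − 0.024) / 0.92 = 0.6261; placebo (0.60 − 0.012) / 0.96 = 0.6125. Spurious difference 1.36 points.

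The standard error at 619 per arm is √(2·0.60·0.40 / 619) = 2.78 points. The two-sided rejection rate is 1 − Φ(1.96 − d/SE) + Φ(−1.96 − d/SE):
- d = 0.99: d/SE = 0.36, giving about 6.5%.
- d = 1.36: d/SE = 0.49, giving 7.8%.

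If f and r are the same in both arms, the two FAS rates are equal and there is no bias. If the two exclusion shares are swapped between the arms, the difference has the same size and favours placebo.

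**The case against.** The strongest reply is that few patients may be affected. *Medication record* is undefined. With dosing three times a day, a patient could have two records on the first day if a record is a dose. *More than one* may also be loose wording for *at least one*, the phrase used for the safety set in Section 2.12.3. The FAS is described only as being as close as possible to the ideal set, not as every randomised patient. Blinding with identical capsules limits exclusion driven by knowledge of allocation, though not exclusion driven by tolerability. All of this stands, and it narrows the point. It does not remove it, because never-treated and unevaluated patients are dropped on either reading, and nothing reconciles the printed rule with Section 2.2.

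Four stronger readings are tempting and lack support:
- *The FAS removes early stoppers as a class.* It does not. Those with two or more records and an evaluation remain.
- *The 10% allowance, 138 of 1,376, is the number at risk of exclusion.* That figure is loss to follow-up. A patient lost after an evaluation at day 30 has a value to carry forward and can stay in the FAS. A patient with a single record and a known D90 mRS is not lost at all. The two groups overlap only in part.
- *The bias favours LSZ.* Nothing in the article indicates which arm would lose more patients, or that those lost would have the worse prognosis.
- *Early deaths are excluded.* Section 2.4 scores death as mRS 6, so an early death may count as an evaluation. The FAS rule does not settle this.

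**Conclusion.** The point holds in a limited form. The rule for the primary analysis set, as printed, departs from the intention-to-treat principle it cites. It contradicts Section 2.2 for patients who stopped after one medication record, and it leaves out early stoppers with no evaluation, whom Section 2.2 says will be followed and included. Never-starters are also excluded, which Section 2.2 does not address. This is a stated rule that needs changing, not a detail left to a fuller document.

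The number of patients affected cannot be derived from the article. The illustrated 1.0 to 1.4 points and type I error of 6.5% to 7.8% rest wholly on assumed two-to-one exclusion and an assumed 30% favourable rate among the excluded. They compare with a planned effect of 9 points. They show that a modest imbalance could matter, and do not forecast that one will occur or in which direction.

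**What to change.** Define the primary analysis set as all randomised patients, analysed as allocated, regardless of medication records. Use every D90 mRS obtained, with death counted as mRS 6, as the scale in Section 2.4 already provides. State how patients with no mRS after randomisation are handled, and add a sensitivity analysis for that choice. Whether last observation carried forward is the right imputation method is a separate question and need not be settled here. Keep the present FAS definition as a sensitivity set, define *medication record* for it, and say whether *more than one* or *at least one* is meant. Bring Sections 2.2 and 2.12.1 into agreement before the interim analysis.

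The cost is mainly wording, since follow-up of early stoppers is already planned. The one statistical downside is a slight dilution of any effect by patients who took little or no drug.

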**FIGURE 1 F1:**
[figure not shown]
The schematic diagram of the patient timeline.

All patients admitted for a course of inpatient rehabilitation following AIS will be recruited and screened for eligibility based on inclusion and exclusion criteria in the study. Also, the study will be advertised on posters in these medical centers, allowing patients to voluntarily contact investigators. Patients will be further screened for study eligibility for AIS treatment through standard admission assessments: comprehensive medical, neurological, and psychiatric histories; reviews of medical records; physical and neurological examinations; reviews of brain imaging reports and electrocardiogram; and pregnancy test only for the premenopausal women. Furthermore, registration data for eligible patients will be collected. Logs of all patients excluded from the study will be retained to document the reasons for exclusion. Screening logs will be submitted to the coordination center monthly. Eligible patients will be informed of the risks and benefits of the study by trained research clinicians. If they agree to participate in the study, patients and/or their legal surrogates will provide written informed consent forms. The intervention will be initiated as soon as possible after randomization. The detailed diagnostic criteria, inclusion and exclusion criteria are presented in Table 1.

**TABLE 1 T1:** Inclusion and exclusion criteria of the LONGAN trial.

Inclusion criteria
Acute ischemic stroke patients within 7 days of onset
18 years of age or older, and gender not limited
NIHSS score of 4–15 at randomization

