### 2.4 Efficacy outcomes

The primary outcome will be the proportion of patients with a favorable outcome, which is defined as mRS ≤1 on D90 (Rankin, 1957). The mRS is an ordinal scale ranging from 0 to 6 (Lees et al., 2012), with 0–1 indicating no disability, 2 to 5 indicating disability (increasing from 2 to 5), and 6 indicating death. The secondary outcomes will be as follows: 1) distribution of mRS scores [will be measured on D30 and D90]; 2) proportion of patients with good functional status [defined as mRS score ≤2; will be measured on D30 and D90]; 3) neurological deficit improvement [defined as a change in the National Institute of Health Stroke Scale (NIHSS) score (Brott et al., 1989), ranging from 0 to 42, with higher scores indicating more severe strokes; will be measured at baseline, D30, and D90]; 4) proportion of poor health-related quality of life (poor-HRQOL) [available EuroQol-5D Questionnaire (EQ-5D) data will be used to calculate EQ-5D index scores (Dorman et al., 1997). Poor-HRQOL is defined as an EQ-5D index score ≤0.5 and will be measured on D30 and D90. The EQ-5D index score is measured on a scale between 0 (death) and 1 (full health). The patient’s mobility, self-care ability, daily activities, feelings of pain or discomfort, and feelings of anxiety or depression contribute to EQ-5D. Here, each aspect will be divided into three levels (Rabin and de Charro, 2001): no problems, moderate problems, or extreme problems. The EQ-5D index score (preference-based health status) will be determined using the population-based preference weight values for five dimensions of the scale (Dolan, 1997; Shaw et al., 2005; Liu et al., 2014). This study will use preference weights applicable to the Chinese population (Liu et al., 2014)]; 5) proportion of patients with functional independence [defined as Barthel Index (BI) ≥90 (Mahoney and Barthel, 1965); BI is a conventional scale used to assess the activities of the daily living of stroke patients involving 10 items with a maximum score of 100 points; will be measured on D30 and D90]; 6) changes in motor function [measured by the Fugl–Meyer Motor Scale (FMMS) score (Fugl-Meyer et al., 1975), ranging from 0 to 100, with lower scores indicating poorer motor status; the change from baseline of the FMMS will be measured on D90]; and 7) changes in cognitive function [measured by the Montreal Cognitive Assessment (MoCA) score (Nasreddine et al., 2005), ranging from 0 to 30, with less than 26 indicating cognitive impairment; the change in MoCA from baseline will be measured on D90].

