### 2.7 Follow-up procedures

The study will consist of four visits, including time of randomization (baseline) and 30, 90, and 180 days after randomization. At baseline, we will evaluate demographic characteristics; routine laboratory test results; computed tomography (CT)/MRI results; electrocardiogram (ECG) results; and NIHSS, Alberta Stroke Program Early CT Score (ASPECTS) (Barber et al., 2000), mRS, FMMS, MoCA, BI and EQ-5D scores. Stroke types will be classified according to the trial of ORG 10172 in acute stroke treatment (TOAST) criteria. At 30, 90, and 180 days after randomization, we will perform assessments using the mRS, NIHSS, FMMS, MoCA, BI and EQ-5D scores. Vital signs and physical examination findings will be recorded at both baseline and 90 days. Finally, medication use for comorbidities and adverse events information will be recorded at whenever they occur during the trial.

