### 2.11 Sample size calculations and interim analysis

The 90-days mRS distribution of the eligible population in The Third China National Stroke Registry (CNSR-Ⅲ) indicates that the proportion of mRS ≤1 is 60.42% (Wang et al., 2019). This study assumes that the proportion of patients with mRS ≤1 in the control group will be 60%, and the proportion of patients with mRS ≤1 in the experimental group will be increased by approximately 15% for a proportion of 69%. According to this assumption and calculations using PASS 11.0 software (NCSS, LLC, East Kaysville, UT, United States), a total sample size of 1,238 in the two groups can achieve 90% power and rule out two-sided type I errors of 5% to detect a superiority margin difference of 5% in this two-arm trial, with an allocation ratio of 1:1. With an estimated loss-to-follow-up rate of 10%, a total of 1,376 participants will be recruited. An interim analysis will be performed when the 50% of recruited patients (619) complete the study. The interim analysis will allow the DSMB to decide whether to continue or terminate the study. Based on the existing data and the expected final sample size, if this study is not expected to obtain efficacious results, the study will be terminated immediately in the current period. For evaluation of the effectiveness of the research, if the research has met the validity standard and meets the requirements of the inspection level, the study can be terminated early. The study will continue if the estimated efficacy is expected to be achieved by the end of the study. If the estimates of the primary outcome in the study (blinded) differ significantly from the actual values, the final sample size allows for appropriate adjustments at the interim analysis.

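### LOCF turns a missing D90 mRS into a D30 mRS in the primary analysis, so unequal loss between arms, or an effect that grows after D30, distorts the treatment difference

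*Protocol article*

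**What the plan says.** Section 2.12.1 of the protocol article fixes the missing-data rule: "Missing data will be imputed using the last observation carried forward (LOCF) method if there are efficacy values after randomization". It applies to the primary endpoint, because "The FAS will be used for primary efficacy analysis in this study". Entry to that set requires that randomized patients "have more than one medication record and evaluation of its efficacy will be included in the FAS".

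Section 2.4 defines the endpoint: "The primary outcome will be the proportion of patients with a favorable outcome, which is defined as mRS ≤1 on D90". Section 2.7 gives the schedule: "At 30, 90, and 180 days after randomization, we will perform assessments using the mRS, NIHSS, FMMS, MoCA, BI and EQ-5D scores". Table 1 admits "Acute ischemic stroke patients within 7 days of onset".

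Three other statements bear on the point:
- Section 2.2 says that patients who stop treatment early are still followed and enter the primary analyses.
- Section 2.11 plans for 10% loss to follow-up overall, with no split by arm.
- Section 2.12.2 foresees sensitivity analyses only if the FAS and per-protocol results disagree. No sensitivity analysis is named for missing data.

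**The concern.** LOCF here needs a post-randomization value, and the only one scheduled before D90 is at D30. The rule therefore replaces the 90-day outcome by one taken at most about five weeks after stroke (30 days plus up to 7 from onset). The trial treats for 90 days and tests functional recovery, so change between D30 and D90 is what it looks for.

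Three consequences follow:
- An arm that loses more patients is pulled further towards its D30 rate.
- A treatment effect that builds up after D30 is diluted even when loss is balanced.
- The filled-in score counts as observed, and the D180 mRS of a patient who missed only D90 is ignored.

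The estimate at stake is that of the primary outcome. The article fixes this rule itself; it is not a detail left to a fuller plan.

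**Working it through.** **Inputs from the article (section 2.11).** Control rate 60%, LSZ rate 69%, two-sided 5%, 90% power, 1:1 allocation, 1,238 evaluable, 10% loss, 1,376 recruited (688 per arm).

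**The plan's own figure.** The pooled two-proportion formula with continuity correction gives 614 per arm, or 1,228, within 1% of 1,238. Without the correction it gives 592 per arm, or 1,184. Inflation: 1,238 / 0.9 = 1,375.6, rounded up to 1,376. The planning inputs can be used as they stand. With 688 per arm and complete data, power for 60% v 69% is 94%.

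**Assumed, because the article does not give them.** The gain in mRS ≤1 from D30 to D90 (g) is 10 to 20 points. The share of an arm with D30 observed and D90 missing (d) averages 10%. All loss falls after D30.

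**Formula.** Expected arm rate under LOCF = (1 − d) × p90 + d × p30. With p30 = p90 − g in both arms, each rate falls by d × g, so

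bias in the difference (LSZ − placebo) = −g × (d_LSZ − d_placebo).

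**Equal loss.** With the same gain in both arms the bias is zero. If the effect is not yet fully present at D30, the estimated difference is 0.90 × 9 + 0.10 × (D30 effect):
- half the effect present at D30: 8.1 + 0.45 = 8.55 points;
- none present at D30: 8.1 points.

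**Unequal loss, no true effect (60% in both arms).**

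| Loss, LSZ v placebo | g | Bias | Two-sided rejection |
|---|---|---|---|
| 12% v 8% | 10 points | −0.4 points | 5.3% |
| 12% v 8% | 20 points | −0.8 points | 6.0% |
| 15% v 5% | 10 points | −1.0 points | 6.6% |
| 15% v 5% | 20 points | −2.0 points | 11.7% |

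Last row in full: the rates become 0.60 − 0.15 × 0.20 = 0.57 and 0.60 − 0.05 × 0.20 = 0.59. SE = √[(0.57 × 0.43 + 0.59 × 0.41) / 688] = 0.0266, and bias/SE = 0.75. Rejection = Φ(−1.96 + 0.75) + Φ(−1.96 − 0.75), about 11.3% + 0.3%. The first part favours placebo, the arm with less loss. In the third row the split is 5.7% and 1.0%. With the loss reversed, the same figures favour LSZ.

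**Unequal loss, planned effect of 9 points, same gain in both arms.**
- 15% on LSZ v 5% on placebo: difference 9 − 1.0 = 8.0 points (g = 10) to 9 − 2.0 = 7.0 points (g = 20); power 87% to 77%.
- 12% v 8%: difference 8.6 to 8.2 points; power 91% to 88%.

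**Part of the loss before D30.** Those patients have no value to carry and leave the FAS. If half the loss falls before D30, 15% v 5% gives carried shares of 0.075/0.925 = 8.1% and 0.025/0.975 = 2.6%. The bias is then 0.55 to 1.11 points and the rejection rate 5.5% to 6.9%.

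**The case against.** The strongest reply is that little will be missing and that loss will be nearly balanced. Section 2.2 keeps following patients who stop treatment, so an adverse event or lack of benefit does not by itself remove the D90 score. The discussion also mentions tele-health visits. The trial is double-blind, and no passage supports a threefold imbalance in loss. This stands: the concern covers only D90 visits that are truly missing, and under moderate imbalance the bias is small against 9 points. It does not remove the point, since the plan still allows for 10% loss and names no safeguard.

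A reader might infer more than the documents support:
- **That LOCF is valid only if nobody changes after D30.** For the difference between arms, equal loss with equal gain gives no bias.
- **That LOCF raises the risk of a false claim for LSZ.** That needs heavier loss on placebo. With 15% loss on LSZ and 5% on placebo, false rejection in favour of LSZ falls to between 1.0% and 0.3%, below the nominal 2.5%.
- **That power falls to 69% to 81%.** Those figures add to the 15% v 5% loss an LSZ effect of only 5 points at D30, so they mix two mechanisms.
- **That capsule burden would drive unequal loss.** Placebo follows the same regimen and matches in appearance, weight and taste (section 2.3).
- **That a living NIHSS, FMMS or MoCA score will be carried past death.** No passage says so; the article is silent. For mRS, death is already 6.

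The FAS wording is also loose. If it required more than one efficacy evaluation, patients with only D30 would be excluded, and bias from exclusion would replace bias from LOCF. That reading does not rescue the rule.

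**Conclusion.** The concern holds in limited form. The mechanism follows from the stated rule and the visit schedule; continued recovery after D30 is a clinical premise consistent with the trial's aim. The direction is not fixed: more loss on LSZ biases against LSZ, and more loss on placebo biases in its favour. Balanced loss protects the difference only if the gain after D30 is the same in both arms.

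The size rests wholly on assumed D30 rates and loss by arm. Distortion is modest at 12% v 8% and becomes serious only at an imbalance such as 15% v 5% with all loss after D30. The rule should still be changed before unblinding, because it sits in the primary analysis and a better method needs no data beyond those already scheduled.

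**What to change.** In section 2.12.1 and the analysis plan:
- Replace LOCF as the primary method by multiple imputation of D90 mRS, done separately by arm, using baseline NIHSS, age, sex, TOAST class, centre, D30 mRS and D180 mRS.
- Keep deaths by D90 at mRS 6, as the scale defines.
- Retain LOCF as a sensitivity analysis, and add a tipping-point analysis on mRS ≤1 that does not depend on whether the FAS and per-protocol results agree.
- State that NIHSS, FMMS and MoCA values are not carried forward past death.

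The cost is analysis-plan wording and standard SAS programming, with no new data. The small downside is that the result then depends on an imputation model, which the tipping-point analysis helps to probe.
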